
**Fig. 2 Fig2:**
[figure not shown]
Outline of the spatial cueing task

#### Stop/signal task

The subsequent task addresses RQ3 and will use a second experimental paradigm involving the same experimental apparatus: a stop/signal task, a variant of the better-known go/no-go task. Whereas the latter requires participants to respond rapidly to a target stimulus (“go”) and withhold a response to a non-target stimulus (“no-go”), the stop-signal task usually requires infrequent withholding of a response when presented with a randomly presented “stop” signal following a choice task between frequent presentations of two “go” stimuli [81, 82]. Also, whilst “go/no-go” tasks have zero stimulus onset asynchrony (SOA), stop/signal tasks have variable SOA. Where the “stop signal delay” (the interval between stimulus presentation and stop signal presentation, i.e. the SOA) is short, participants can easily inhibit a response. With longer delays, participants are more likely to execute a response and, thereby, have failed to inhibit. The stop-signal task, then, represents a more difficult test of response inhibition than go/no-go tasks due to the increased likelihood of a pre-planned response being executed when there is more time for execution, in combination with the higher frequency of “go” versus “stop” signals.

The “Horse Race Model” [82–84] is a theoretical explanation for performance on the stop/signal task, where go and stop processes are deemed independent and “race” each other to their respective thresholds and, thereby, to one of two outcomes: a response or response inhibition. By varying the SOA (between the “go” choice stimuli and “stop” signal: termed “staircasing”), a time estimate for response inhibition can be calculated from the mean SOA required for a 50% success rate of response inhibition and the mean RT to Go stimuli. This is the “stop-signal reaction time” (SSRT). The current study will be based on a key study of *emotional* inhibition undertaken by Verbruggen and De Houwer [35].

These authors reported that when using an emotional target stimulus in a stop/signal task, compared with neutral stimuli, this resulted in slower RTs due to increased emotional activation (i.e. greater task interference from emotional stimuli). The current study will vary from their approach somewhat in that the Verbruggen and De Houwer also investigated differences in impact from varying valence and intensity of imagery (finding only an effect from the latter), whereas the current study seeks to compare levels of inhibition to arousing stimuli of *either* valence, and using neutral stimuli for similar reasons to the spatial cueing task (as a standard control for the sudden onset of a visual presentation). Using an array of valence scores aims to support a more general emotional effect (which the study on spatial cueing is not able to do given the need to maximise high arousal stimuli).

The full procedure will run as follows:

Instructions are provided on-screen for the practice block. This training block consists of 24 trials using 8 neutral IAPS/NAPS images, otherwise following the same process as for the experimental phase. For the experimental phase (8 blocks of 60 trials), 120 images will be used (40 positive, 40 negative, 40 neutral), with each image appearing four times. The set of 120 images (see Additional file 2) will be split into two halves, with half presented in even numbered trials, and the other half in odd numbered trials.For all blocks, participants first fixate on a cross at the centre of the screen for 500 ms (Fig. 3); IAPS/NAPS stimuli are then presented for another 500 ms.On “go” trials, participants must respond to the visual stimuli “#” or “@” presented at the centre of the screen, pressing a corresponding key as quickly and accurately as possible after presentation. These symbols will be reproduced as stickers on the keyboard to ensure participants make the required key press. Responses must be completed within 1250 ms before the next trial begins. After incorrect trials, this ISI begins following a 250 ms delay. The word “Incorrect” appears when there is an error, “Respond” if there is no response when there should be, and “Stop” where there is a response but should not be.On “stop” trials (indicated by a tone on headphones; 750 Hz, 50 dB, 100 ms; presented randomly in 30% of trials = 48 stop trials per valence set), participants must withhold a response to the visual stimulus. The stimulus onset asynchrony (SOA; the stop-signal delay) between the choice task stimulus and the auditory tone will begin at 250 ms, then vary by staircasing: a response on a “stop” trial results in a decrease in the SOA by 50 ms, successfully withholding a response on a “stop” trial results in an increase of 50 ms.Participants will be informed of this auto-adjustment in staircasing, to discourage their anticipation of the “stop” signal and to focus only on rapidly responding to the symbols (as emphasised in Verbruggen and De Houwer).If in the unlikely event a participant presses before the tone, a neutral message of “Next trial” appears on-screen in order to ensure that random, rapid key pressing is discouraged whilst at the same time not penalising genuine attempts to respond rapidly. (This is a bespoke part of the design, not taken from Verbruggen and De Houwer.)The time between trials will be 1500 ms.At the end of each block, performance feedback is provided to participants: the number of correct “go” responses (i.e. pressing the correct symbol), number of incorrect “go” responses (i.e. pressing the wrong symbol), number of incorrect “go” non-responses (i.e. too slow), number of correct “stop” non-responses (i.e. withholding a response when hearing a tone), and number of incorrect “stop” responses (i.e. responding in the presence of a tone). Trials where “Next trial” appears on-screen are not included in this tally.There will be a 30-s gap between blocks.

**Fig. 3 Fig3:**
[figure not shown]
Outline of stop/signal task

#### Counterbalancing

For half of the participants in each group (assigned at random), the blocks will be presented in the order 1–8; the order will be 8–1 in the other half.

#### Measuring interoception

Towards the end of each laboratory visit, measures of interoception will be taken. Interoceptive sensitivity will be assessed using two different methods.

#### Schandry heart tracking task [85]

This will be undertaken by all participants, again using *SuperLab* and *Labchart* with *PowerLab*. This entails a participant counting their heart beats within set time periods (a training interval of 25 s, followed by four experimental intervals of 25, 35, 45, and 55 s presented in random order) without taking their own pulse or using any other non-visceroceptive cues (e.g. hearing their heart beat, watching a part of their body pulse in tandem with heart beat) at the same time as the actual heart rate is measured using ECG. The onset of each time period is signalled by a single tone played through headphones, with the offset of each period signalled by a double tone (200 ms gap between two single tones). Participants will then type in their estimated number of heart beats. Each counting period will be separated by a 30-s interval. For ECG recordings, the single and double tones will be used as reference points to permit the calculation of difference between actual heart rate and perceived heart rate, as a measure of interoceptive sensitivity (accuracy).

#### Water load test [86]

After disconnecting from the ECG and computer, the water load test will be undertaken by all participants. This has two stages: the first stage entails participants’ self-assessment of having reached a state of satiation following drinking water from a 5-L glass container through a 4.8-mm clear PVC 1 m tube. The glass containers will be covered to prevent participants from knowing the volume of water in each, to give a sense of a practically unlimited supply of water. Unknown to participants, each flask contains no more than 1.5 L of water. This limitation on the amount of water prevents the risk of water intoxication, in combination with the screening measures in place regarding kidney health. Further, in addition to the previous use of this task in published, peer-reviewed research, this component was deemed safe from consultation with an endocrinologist and following the University ethics process. Further, this was confirmed by a second physician (who will provide oversight of the project in general).

The second stage entails drinking water from an identical set of apparatus until reaching a sense of fullness. In the original paradigm, each participant was not informed about this subsequent stage until after the first stage was complete. However, given that this measure will be repeated over two data points, participants will be informed about the second stage prior to the onset of the task to ensure consistency across data points^3^. Each stage of the task is limited to 5 min. The amount of water consumed at each stage—measured by weight differences of the containers between pre- and post-consumption of water—is then used to calculate the participant’s interoceptive sensitivity to gastric sensations. Due to the fact that having a full stomach of water would likely confound measurement during the previous tasks (not least due to relative discomfort), this measure of interoception will be taken towards the end of each laboratory visit. Also, running the water load test at the end (approximately 2 h into their visit) also helps to ensure greater parity between participants in terms of prior water intake.

Finally, each participant will complete a brief self-report questionnaire to measure interoceptive sensibility (The *Multidimensional Assessment of Interoceptive Awareness* or MAIA [87]). This is outlined in the next section.

In undertaking measures of sensitivity and sensibility, this also allows the calculation of metacognitive awareness; in this way, all three forms of interoception can be measured [88].

After the 8-week intervention period, participants will attend the follow-up, involving repetition of all procedures outlined above. Participants will be reminded at the start of the second visit that all procedures will be identical and to perform them as at baseline.

## Descriptions of self-report tools for outcome measures (emotion regulation and interoceptive sensibility)

The *Difficulties in Emotion Regulation Scale* (DERS) consists of 36 items (reduced to 18 in a validated short version [89]) in six subscales [90]: (i) non-acceptance of emotional responses, (ii) difficulties engaging in goal-directed behaviour, (iii) impulse control difficulties, (iv) lack of emotional awareness, (v) limited access to emotion regulation strategies once an emotion is in process, and (vi) lack of emotional clarity. (See, for example [91] for information on the scale’s psychometric properties.) A key rationale for using a tool such as this is to assess how the measures taken in the laboratory (i.e. at an early stage during an emotional reaction) may relate to later stage emotion regulation. For instance, decreased RTs in the spatial cueing task may indicate increased access to emotional sensations and which may relate to emotion regulation.

The *Emotion Reactivity Scale* (ERS) consists of 21 items in three subscales (i) the sensitivity to emotion (e.g. “Other people tell me I’m overreacting”), (ii) intensity (e.g. “When I experience emotions, I feel them very strongly/intensely”), and (iii) persistence (e.g. “When something happens that upsets me, it’s all I can think about for a long time”). (For information on the scale’s psychometric properties, see [92]). Regarding this measure, according to some theorists, the primary reason given for the decision to attempt suicide is to escape from aversive and intolerable emotion [93–96], which may result from increased emotional reactivity associated with some psychological disorders [92]. The rationale for the use of the ERS in the current trial is the same as for the DERS.

The *SF-36* is a short-form health questionnaire. For the purposes of the current project, several sub-scales have been chosen to track physical and mental wellbeing over time: Physical Functioning; Emotional Well-being; Pain; General Health (see https://www.rand.org/health-care/surveys_tools/mos/36-item-short-form.html; RAND Corporation).

The *Multidimensional Assessment of Interoceptive Awareness* [87] (MAIA) is a 32-item questionnaire involving 8 scales: (i) Noticing: awareness of uncomfortable, comfortable, and neutral body sensations; (ii) Not-Distracting: tendency not to ignore or distract oneself from sensations of pain or discomfort; (iii) Not-Worrying: tendency not to worry or experience emotional distress with sensations of pain or discomfort; (iv) Attention Regulation: ability to sustain and control attention to body sensations; (v) Emotional Awareness: awareness of the connection between body sensations and emotional states; (vi) Self-Regulation: ability to regulate distress by attention to body sensations; (vii) Body Listening: active listening to the body for insight; and (viii) Trusting: experience of one’s body as safe and trustworthy. One advantage of using the MAIA is that it is able to differentiate between interoceptive sensibility that is linked to “somatization” (a problematic hyper-awareness of the body) and interoceptive sensibility linked to well-being.

## Variables

### Predictor variables (both tasks)

Group membership ([interoception groups] vs. [control];Data point/time (baseline vs. follow-up);Interoceptive accuracy/sensitivity (continuous measure);Interoceptive sensibility (continuous measure);Interoceptive metacognitive awareness (continuous measure);Heart phase ([systole] vs. [diastole]);Valence of emotional stimuli ([positive: *stop/signal task only*] vs. [negative] vs. [neutral]).

### Predictor variables (spatial cueing task only)

Presence/absence of emotional stimulus (i.e. “catch” trials);Cued position on body in the spatial cueing task ([shins] vs. [chest] vs. [lower abdomen]; or [a part of the body cued] vs. [no part of the body cued]);

### Dependent variables (both tasks)

*Primary outcome*: RTs;Scores on self-report measures;Heart rate variability, heart rate deceleration.

### Dependent variables (spatial cueing task only)

Frequency of response to emotional stimuli;Intensity of experience (continuous);Valence reported ([positive] vs. [negative] vs. [neutral]);Location of felt experience (point indicated on a human model; to be coded into a categorical measure).

## Hypotheses

Based on the foregoing detail, the hypotheses for the studies are as follows:

### Spatial cueing task

One of the interoception groups will show significantly faster reaction times (RTs) and greater response frequency to emotional stimuli regardless of cue type compared with each of the other groups after baseline; plus, there will be a greater change between baseline and follow-up. Each of the interoception groups separately and combined will show significant differences from the control group.One set of cues for the same group (i.e. the interoception group in (1)) will facilitate significantly faster RTs and greater response frequency. This set will match the target area of the body for that group (i.e. a chest cue for the cardioception group; a lower abdomen cue for the gastroception group). The “matching” cue for the other interoception group will not facilitate faster RTs or greater response frequency. If any cue facilitates faster RTs or greater response frequency for the other groups, it will be the same cue that facilitates for the interoception group in (1).This same group will display greater within-group coherence in the location of the body indicated to be active during trials compared with the other groups after baseline. It will also show the greatest change between baseline and follow-up compared with the other groups.This same group will report greater intensity compared with the other groups after baseline. It will also show the greatest change between baseline and follow-up compared with the other groups. The interoception groups combined will report greater intensity than the control group.This same group will show greater heart rate deceleration after baseline following the presentation of emotional stimuli compared with the other groups; both interoceptive groups will show greater heart rate deceleration than the control group.

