**Fig. 1 Fig1:**
[figure not shown]
Trial overview

Since emotion research deals with constructs that are multiply realised [24], the project will employ multiple measures. There will be two primary, single-blinded studies, both laboratory-based, one utilising a spatial cueing task and another utilising a stop/signal task. In addition, physiological and self-report measurements will be taken (these are described in detail below).

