### Stop/signal task

6.This same group will show significantly slower RTs on the stop-signal task after baseline and a greater change in RTs between baseline and follow-up compared with the other groups, but with each of the interoceptive groups separately and combined showing significantly slower RTs compared with the control group.

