### Hypotheses on interoception and emotion regulation:

7.Both interoceptive groups will show increases in interoceptive sensitivity (measured by the Schandry task and water load test), sensibility (measured by the MAIA), and metacognitive awareness over the study period, but there will be no significant differences between each other either at baseline or between baseline and follow-up. They will each be significantly different from the control group on these measures. Further, the cardioception group will show the greatest improvement on the Schandry task, and the gastroception group will show the greatest improvement on the water load test.8.The two experimental groups will each show significant improvements over the control group on the *DERS*, the *ERS*, and the *SF-36* (emotional well-being sub-scale) scores between baseline and follow-up, with the same group as in (1) showing greater improvements compared with both of the other groups.

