## Data analysis

Generalised Estimating Equations (GEE) will be used to analyse the two data points, including variable interactions. GEE can account for repeated measures as well as the potential problem that the primary outcome variable (RT) may not be normally distributed (although it will be continuous). Using GEE, the effects of the predictors on RT can be modelled under different circumstances, and the interrelationships between predictors can also be investigated. Significance testing will be undertaken at the *p* < 0.05 level.

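### Hypotheses 1 and 6 make many separate significance claims on RT at an unadjusted 0.05, with no primary contrast named and the leading group left to the data

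*Protocol article*

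**What the plan says.** - **Primary outcome.** The list of dependent variables for both tasks gives "Primary outcome*: RTs". The Design section adds that "There will be two primary, single-blinded studies, both laboratory-based", namely spatial cueing and stop/signal. No task, contrast or time form is ranked above another.
- **Hypothesis 1 (spatial cueing).** "One of the interoception groups will show significantly faster reaction times (RTs) and greater response frequency to emotional stimuli regardless of cue type". The claim is made against both remaining arms, at follow-up and as change from baseline. It continues: "Each of the interoception groups separately and combined will show significant differences from the control group".
- **Hypothesis 6 (stop/signal).** "This same group will show significantly slower RTs on the stop-signal task after baseline", with a greater change than the other groups. Each interoception group, and both combined, are also to be significantly slower than control.
- **Carry-over.** Hypotheses 2 to 6 refer back to the group identified in hypothesis 1. Hypothesis 8 does so too, "with the same group as in (1) showing greater improvements compared with both of the other groups".
- **Decision rule.** The Data analysis section says: "Significance testing will be undertaken at the *p* < 0.05 level". It gives no order, hierarchy or adjustment.
- **Sample size.** The calculation covers one group-by-time effect on spatial-cueing RT.

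**The concern.** The protocol fixes a significance level and a list of significance claims, but not the claim that decides the trial. Two primary RTs, four group contrasts and two time forms give many routes to a significant RT difference, and each is worded as a result in its own right. If any one of them is taken as support, the real error rate is well above the stated 0.05.

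A second, smaller problem is that the favoured group is read from the results. A win for chest or for abdomen would fit hypothesis 1 equally well. Later hypotheses are then tested on a group selected with the same participants' data, so they are not independent confirmation.

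**Working it through.** **The plan's own figure.** Partial eta-squared 0.15 gives f² = 0.15/0.85 = 0.1765. With N = 54, λ = 0.1765 × 54 = 9.53. A 2-df large-sample chi-square test at 0.05 then has 79.5% power, so 54 is reproduced to within rounding. The F test with 51 denominator df gives 77.0% and would need 58, which the target of 70 with at most 10 drop-outs covers. This calculation is for one overall test, not for the contrasts below.

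**Inputs from the protocol.** Alpha 0.05 (Data analysis); three groups at 1:1:1 (Randomisation); (70 − 10)/3 = 20 per group (Sample size); RT in two tasks (Dependent variables).

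**Assumptions.** Two-sided tests; pre-post correlation 0.5 (0.3 to 0.7 also tried); correlation between outcomes 0 to 0.5; no true effect anywhere.

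**Contrasts.** With C = cardioception, G = gastroception and K = control, these are C − G, C − K, G − K and (C + G)/2 − K. Each is tested by t = Σw·mean / √(s²·Σw²/n) on 57 df, once on follow-up values and once on follow-up minus baseline.

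**Chance of at least one p < 0.05** (15,000 to 20,000 simulated null trials):

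| Tests counted | Number | Chance |
|---|---|---|
| One RT, one time form | 4 | 0.13 |
| One RT, follow-up and change | 8 | 0.21-0.23 |
| Both RTs, one time form | 8 | 0.22-0.24 |
| Both RTs, follow-up and change | 16 | 0.37-0.40 |
| The 16, control contrasts counted only in the predicted direction | 16 | 0.27-0.29 |
| The 16 plus cue-specific RT tests (hypothesis 2) | 18 / 22 | 0.44-0.45 / 0.52-0.53 |
| The 16 plus response frequency | 24 | 0.47-0.53 |

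If the tests were independent, 1 − 0.95^k would give 0.19, 0.34 and 0.56 for k = 4, 8 and 16. The simulated values are lower because the contrasts share groups and data.

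**Effect of leaving the group unnamed.**
- Either group beating control in the predicted direction: 0.044-0.046, against 0.025 for a group named in advance.
- One group beating both others at follow-up: 0.009-0.010, against about 0.005.
- Picking the winner on follow-up RT, then testing another outcome against the other interoception group: nominal 0.025 rises to about 0.04 if the outcomes correlate 0.3 and 0.046 if 0.5. There is no inflation at zero correlation.

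**Hypothesis 1 as a conjunction.** One group beating both others on RT, at follow-up and in change, occurs about 0.001 of the time or less.

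**What an adjustment would do.** Bonferroni over the 4 contrasts on one RT gives about 0.035; over all 16 on both RTs, about 0.036.

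**The case against.** **Hypothesis 1 is a conjunction.** Read as a whole, it asks one group to beat each other group, after baseline and in change. That is rarely met by chance. This stands, and limits the finding: the inflation arises when a single significant contrast is reported as support. The protocol does not say that it will be used that way. But it also does not say that all parts must hold, and it words the control contrasts as significant differences in their own right.

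**The count is a reading.** The control contrasts are stated once in each hypothesis, and applying both time forms to all of them is an interpretation. Directional counting also lowers the figure. Both points stand, which is why a range is given; its lower end, 0.13, is still more than twice 0.05.

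**A coin toss.** A reader might infer that a false positive on a primary measure is about as likely as not. The documents do not support that. Response frequency is listed separately and is not labelled primary, and without it or the cue-specific tests the figure for both RTs stops at about 40%.

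**The unnamed group as main cause.** A reader might also infer that a freely chosen winner leaves the central claim with no error control. The selection effect is small beside the number of contrasts, and hypothesis 1 itself requires the winner to be significantly faster than each other group. Localisation is tested by hypotheses 2 and 3, not by hypothesis 1.

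**A separate analysis plan may adjust.** It may, and a missing adjustment alone would be no finding. The point rests on what the protocol does state: RT as primary in two tasks, a list of significance claims, one unadjusted level and a group not named. A later Holm step would not name the group.

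**Conclusion.** The concern holds in limited form. The protocol fixes multiple significance claims on its primary outcome at an unadjusted 0.05, with no primary contrast. If any one significant contrast counts as support, the false-positive chance is about 13-23% for one RT and about 22-40% across both. It is about 50% only when response frequency or cue-specific tests are added.

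These figures assume no true effect, 20 per group, two-sided t-tests and a pre-post correlation of 0.5; correlations of 0.3 and 0.7 change them little. The number of contrasts is the main cause and the unnamed group a smaller one. The trial is described as preliminary, which tempers the consequences but does not remove the need to say which test decides.

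**What to change.** 1. Name one primary test at 0.05: the interoception groups combined versus control on spatial-cueing RT at follow-up, adjusted for baseline RT. This one test replaces the separate after-baseline and change comparisons.
2. Make a two-sided cardioception-versus-gastroception test on the same outcome the gatekeeper. Test the claims in hypotheses 2 to 6 and 8 about the same group only if it is significant; otherwise report both groups with confidence intervals.
3. Make stop/signal RT a key secondary outcome, and apply Holm to the remaining pairwise contrasts and to response frequency.
4. State that group is modelled with three levels. The predictor list groups the interoception arms against control, whereas the Design and Sample size sections describe three groups.

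The change is to analysis wording only. It costs some power on the secondary contrasts, and the claims about a single favoured group become descriptive if the gatekeeper is not passed. The primary test keeps the full 0.05. Splitting alpha 0.025/0.025 between the two tasks is not advised, because it would reduce power on the primary test.
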